### Procedures

Patients who schedule an appointment at any of the participating falls clinics (i.e., intervention and control hospitals) will receive a letter containing information on the objectives and procedures of the study and an invitation to participate. For patients in the intervention arm, the invitation letter will also include a printed QPL and a link to the patient portal.

At the falls clinic, eligibility will be determined according to the in- and exclusion criteria by the hospitals’ staff members. The researcher will then provide oral and written information about the study to eligible patients. Patients who are interested in participating in the study will be asked to sign an informed consent form. Next, the falls clinic assessments will be carried out as usual. In the intervention group, the physician will use the CDSS prior to the consultation to understand a patient’s fall risk and medical background as well as during the consultation with the patient. Consultations in the control group are carried out according to care as usual. After the consultation, the research assistants will ask the included patients and their caregivers (if applicable) to fill out a set of questionnaires (see “Data Collection”). After the visit to the falls clinic, patients in the intervention group will be able to review information about their consultation with the physician (i.e., their treatment plan) and their estimated fall risk in the patient portal.

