### Data management

Data will be handled confidentially and only a limited number of members of the study team will have access to the complete datasets. The collected and pseudonymized questionnaire data for each local center will be transferred to the Amsterdam UMC, where it will be entered, stored and processed in Castor. In addition, the digital CDSS and patient portal data will be stored locally at each hospital. Every 3–6 months, study data will be extracted to.csv text files and stored in a secured folder. Furthermore, administrative data will be stored in a secured SQL database. Finally, data from both control and intervention patients will be extracted from Epic every 3–6 months to.csv text files (e.g. medication data, problem lists, relevant lab values, and the prediction model variables). Data from individual patients will be pseudonymized, and the different datasets can only be linked through a participant identification number, which is stored in a separate data system. These data management systems all comply in accordance with the European Union General Data Protection Regulation.

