### Statistical analysis

Data of the RCT will be analyzed according to the intention-to-treat principle. P-values of < 0.05 will be considered statistically significant.

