### Estimating the effectiveness of the intervention on trial outcomes

For every participant, we will assess fall incidents during a fixed follow-up period of 12 months, which will start after a set 1 month, during which the dose of FRIDs will be stopped or decreased. Difference in time to injurious fall between the intervention and control group in the follow-up period will be analyzed by means of a multilevel Cox regression model based on hospital level [69]. Model fit will be assessed using standard approaches (e.g., the proportional hazards assumption with Schoenfeld residuals). We will adjust all models for age, sex and type of hospital, i.e. academic versus non-academic. In a sensitivity analysis, we will additionally adjust for significant baseline differences. Difference in total number of (injurious) falls in the follow-up period between the control and intervention groups will be analyzed by means of multilevel Poisson regression models based on hospital level. In the case of overdispersion, we will apply either quasi-Poisson regression or negative binomial regression depending on the observed distribution of the data. Difference between the intervention and control group with respect to time to any fall and time to fall that results in any injuries will be analyzed by means of survival analyses, similarly to the primary outcome.

Differences in EQ-5D-5L index score, EQ-5D visual analogue scale, and TOPICS-SF summary score between the intervention and control group after 12 months will be analyzed by means of linear mixed models. These models will be adjusted for the baseline value of the outcome [70].

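### The sensitivity analysis chooses its covariates by baseline significance tests; a short pre-specified list of prognostic covariates should replace that rule

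*Protocol article*

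**What the plan says.** The effectiveness part of the Statistical analysis section of the protocol article fixes the covariates of the main models: "We will adjust all models for age, sex and type of hospital, i.e. academic versus non-academic". It then adds one further analysis: "In a sensitivity analysis, we will additionally adjust for significant baseline differences". No variables are named for it. The opening of the same section sets the threshold, "P-values of < 0.05 will be considered statistically significant", and the natural reading is that this also defines a significant baseline difference. The article does not say whether the baseline tests would allow for clustering by hospital.

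The Data management section shows that candidate predictors are available in both arms: "data from both control and intervention patients will be extracted from Epic every 3–6 months", with examples that include "medication data, problem lists, relevant lab values, and the prediction model variables". The Background names fall history, impaired mobility, frailty, chronic conditions, fear of falling, depression and cognitive impairment as risk factors, alongside age and sex.

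Two design features bear on how far the arms may differ at baseline. Under Randomization and blinding, hospitals are allocated before inclusion starts, without blinding, and two of them are assigned to an arm by default. Under Procedures, intervention patients get different material before consent: "the invitation letter will also include a printed QPL and a link to the patient portal".

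**The concern.** A covariate distorts a treatment comparison only if it is both imbalanced and prognostic. A baseline test looks at imbalance alone, and only relative to its sampling error. Selecting on that test has three consequences:

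- A moderate imbalance in a good predictor is left out because it is not significant.
- A difference in an irrelevant variable is brought in because it is significant, and more often so if the test treats patients within a hospital as independent.
- The covariate set is unknown until baseline data have been compared by arm, so the analysis is not pre-specified in the sense that matters.

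The adjusted analysis carries more weight in this trial than in many others. With few hospitals, two not randomized, and staff and patients aware of the arm at enrolment, differences in case mix may be more than chance. Readers will turn to this sensitivity analysis to judge whether case mix explains the result.

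**Working it through.** **Inputs from the Sample size section.** 385 analysed per arm, ten clusters of 77, outcome ICC 0.01, proportions 0.22 and 0.12, two-sided 5%, 80% power, 10% drop-out, 856 in total.

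**Assumed, because the article gives no value.** Covariate ICC of 0.01 or 0.05; predictor HR of 1.5 per SD (log HR 0.405), with a range of log HR 0.3 to 0.7 per SD.

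**Step 1: the plan's own figure.** The two-proportion formula gives 221 per arm (pooled variance) or 217.6 (unpooled). The design effect is 1 + (77 − 1) × 0.01 = 1.76. Then 221 × 1.76 = 389 and 217.6 × 1.76 = 383, which bracket the stated 385. Drop-out: 770 / 0.90 = 855.6, so 856. The sample size reproduces. Under proportional hazards the design effect size is HR = ln(0.88) / ln(0.78) = 0.5145, a log HR of −0.66.

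**Step 2: what the rule can miss.** The largest standardized difference that is not significant is 1.96 × √(2/385) = 0.141 SD. If the test allows for a design effect of 1.76, it is 1.96 × √(1.76 × 2/385) = 0.187 SD.

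- At HR 1.5 per SD: 0.141 × 0.405 = 0.057 on the log scale; exp(0.057) = 1.06, a shift of about 6%.
- Over log HR 0.3 to 0.7: 0.042 to 0.099, which is 6% to 15% of the design log HR. At 0.187 SD it is 0.056 to 0.131, or 8% to 20%.

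**Step 3: what the rule can flag by chance.** If a patient-level 5% test ignores clustering, its false-flag rate is 2 × [1 − Φ(1.96 / √(1 + 76 × ICC))].

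- ICC 0.01: 1.96 / √1.76 = 1.477, giving 14%.
- ICC 0.05: 1.96 / √4.8 = 0.895, giving 37%.
- At least one false flag among ten independent covariates: 1 − 0.95^10 = 40% for a valid test; 1 − 0.86^10 = 78% at ICC 0.01 with clustering ignored.

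**Step 4: consequence for inference.** A simulation used five against five hospitals of 77 patients, a constant-hazard model, cluster-robust standard errors, t with 8 df and 1,500 runs per setting. It compared no covariate, a covariate added only if significant at baseline, and the covariate always included. Power (%) at log HR −0.665:

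| Log HR per SD | Covariate ICC | No covariate | Added if significant | Always included |
|---|---|---|---|---|
| 0.3 | 0.01 | 73.1 | 73.5 | 73.6 |
| 0.3 | 0.05 | 71.9 | 72.9 | 73.3 |
| 0.5 | 0.01 | 72.5 | 72.8 | 74.5 |
| 0.5 | 0.05 | 68.1 | 69.8 | 72.9 |
| 0.7 | 0.01 | 68.7 | 69.3 | 73.0 |
| 0.7 | 0.05 | 63.9 | 68.6 | 74.4 |

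Always including the covariate gains about 0 to 2 points over no covariate for a modest predictor (0.3) and about 4 to 10 for a strong one (0.7). Under no effect, rejection rates were 3% to 6% for all three strategies. Two limits apply: the simulated imbalance arises by chance only, and the comparison model holds no age, sex or hospital type.

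**The case against.** The strongest reply is one of scope. The rule governs a single sensitivity analysis. The primary covariates are pre-specified, include the stratification factor, and contain two risk factors that the article itself names. A short list of this kind is defensible. A reader might infer that the significance rule biases the primary estimate, or that strong predictors have been wrongly shut out of the primary model. The article supports neither inference. The rule never reaches the primary model, no predictor effect sizes are given, and any prediction-model variable that differed significantly would enter the sensitivity model.

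The magnitudes are also conditional. The ICC of 0.01 is the outcome's, borrowed here for covariates, and 0.05 is not in the article. The 14% and 37% need a test that ignores clustering, which is not stated. The 6% is an edge case: the largest unflagged imbalance, in a predictor that does not overlap with age or sex. On the plan's figures there would be 385 × 0.22 = 84.7 and 385 × 0.12 = 46.2 events, so the standard error of the log HR is about √(1.76 × (1/84.7 + 1/46.2)) = 0.24. A shift of 0.057 is about a quarter of that. Over-flagging a harmless covariate does little damage in a secondary analysis.

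Finally, a reader might take covariate adjustment as the answer to recruitment after allocation. It removes only the part of any selection that shows in measured variables.

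All of this stands, and it limits the size of the point. It does not defend the rule, which the article fixes in its own text and so has not left open for an analysis plan to settle.

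**Conclusion.** The point holds for the sensitivity analysis. Choosing covariates by baseline p-value ignores prognostic strength and makes the model depend on the data. It can leave out an imbalance of up to about 0.14 SD, which is about 6% on the treatment HR if the predictor has an HR of 1.5 per SD. It over-flags if clustering is ignored (14% or 37% under the two assumed covariate ICCs). It does not alter the primary estimate and did not inflate type I error in the settings simulated, where imbalance was due to chance.

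Enriching the primary model is a recommendation and not the correction of an error. The gain depends on assumed predictor strength and is modest. The point is worth acting on because this is the analysis that readers will use to judge case-mix differences between ten hospitals, two of them not randomized, with enrolment after allocation is known.

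**What to change.** Delete the significance rule. Before outcome data are seen, name a short list of patient-level prognostic covariates measured before the consultation. Candidates are the prediction-model variables or score, extracted for both arms, or fall history and number of fall-risk increasing drugs. Use this list in the sensitivity analysis in place of the rule. Preferably also add it to the primary Cox model and the count models, and report the model with only age, sex and hospital type alongside. Keep hospital-level covariates few, given ten clusters. The planned 856 patients do not change.

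Costs and cautions:

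- Missing predictor values will need imputation; their completeness is not known from the article.
- The routine extraction runs every 3–6 months, so the list must fix the time point and use pre-consultation values only.
- The prediction model was still being externally validated at publication, which favours naming its variables as a fallback to the score.
- Eligibility already requires at least one fall in the past year and use of at least one such drug, which narrows the spread of the simpler alternative. The text shown does not confirm that a count of past falls is recorded.
- Changing the primary model needs a documented amendment, and it changes the conditional HR being estimated. Replacing the rule in the sensitivity analysis alone is a change of wording.

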### Estimating the cost-effectiveness of the intervention

Differences in costs and effects between intervention and usual care will be estimated using seemingly unrelated regression to retain the correlation between costs and effects. Incremental cost-effectiveness ratios will be calculated by dividing the difference in costs between CDSS and usual care due to differences in incidence in injurious falls as well as gained quality-adjusted life years (QALYs). Bootstrapping techniques will be used to estimate the uncertainty surrounding the incremental cost-effectiveness ratios. Uncertainty will be shown in cost-effectiveness planes and cost-effectiveness acceptability curves.

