### Randomization and blinding

Since the intervention needs to be integrated into the physician’s workflow, randomization will be performed at hospital level prior to the start of inclusion. We evaluated use of the CDSS in usability studies among physicians of one of the locations of the Amsterdam UMC, i.e. location AMC. To avoid possible contamination of the intervention, the Amsterdam UMC: location AMC will be exempted from randomization and included in the intervention group by default. To assure the control and intervention hospitals remain similar with respect to their patient population, the other location of Amsterdam UMC, i.e. location VUmc, will be included in the control group by default. Randomization of the remaining hospitals will be done based on a 1:1 allocation ratio and stratified based on whether the hospital is academic or non-academic. The randomization procedure will be done by an independent statistician using computer-generated random numbers. Blinding of the intervention allocation is not possible since both physicians and patients will have to interact with the CDSS and patient portal. Researchers will be blinded to group allocation during the statistical analyses.

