### Sample size

Sample sizes of *n* = 385 in the intervention and *n* = 385 in the control group (10 clusters with 77 patients in each cluster) are needed to detect a difference in proportion of injurious falls of 0.10 with 80% power. We inferred the proportion of patients who will experience an injurious fall to be 0.22 in the control and 0.12 in the intervention group. In these calculations, we assumed the two-sided significance level of 5% and an intraclass correlation coefficient of 0.01 to account for clustering [71]. Presupposing a drop-out rate of 10%, 856 patients will need to be included.

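### The cost-effectiveness analysis names seemingly unrelated regression and a bootstrap with no hospital level; run on patients as named, it would understate uncertainty in a trial allocated by hospital

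*Protocol article*

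**What the plan says.** Under Statistical analysis, the protocol article's section on estimating cost-effectiveness states that cost and effect differences "will be estimated using seemingly unrelated regression to retain the correlation between costs and effects". It continues: "Bootstrapping techniques will be used to estimate the uncertainty surrounding the incremental cost-effectiveness ratios". And: "Uncertainty will be shown in cost-effectiveness planes and cost-effectiveness acceptability curves". The effects entering the ratios are injurious falls and QALYs. The section names no hospital term, cluster-robust variance or resampling unit.

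The rest of the article treats the trial as clustered:

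- Randomization and blinding: "randomization will be performed at hospital level prior to the start of inclusion".
- Sample size: 10 clusters of 77 patients, 385 per arm, with "an intraclass correlation coefficient of 0.01 to account for clustering".
- Estimating the effectiveness of the intervention (statistical analysis): multilevel Cox regression for time to injurious fall and multilevel Poisson regression for fall counts, both at hospital level. Quality-of-life scores get linear mixed models, with no grouping level named.
- Process evaluation, shared decision making (statistical analysis): multilevel modelling of the between-arm differences.

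**The concern.** The article gives one reason for choosing SUR: to keep the correlation between costs and effects. That correlation lies between two outcomes of the same patient. The design creates a second one, between different patients treated at the same hospital, and standard SUR has no element for it. A bootstrap that resamples patients has none either. An analyst who follows the section as written could reasonably fit SUR to patients and resample patients.

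Cost-effectiveness is a declared secondary aim, and the article foresees wider implementation if the intervention proves effective. The planes and acceptability curves are what a decision-maker would read, and they would show too little spread. The trial could also report two precisions for closely related quantities: injurious falls from a multilevel model in the effectiveness analysis, and injurious falls from a patient-level model in the economic one.

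**Working it through.** **Inputs.** From the Sample size section: proportions assumed "to be 0.22 in the control and 0.12 in the intervention group", two-sided alpha 0.05, power 80%, ICC 0.01, 77 patients per cluster, 385 per arm, 10% drop-out, 856 in total. Hospitals per arm: 385 / 77 = 5. The article gives no ICC for costs or QALYs.

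**Step 1: reproduce the protocol's own figure.**

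- Unpooled variance, no clustering: n = (1.96 + 0.8416)² × (0.22 × 0.78 + 0.12 × 0.88) / 0.10² = 217.6 per arm. The pooled-variance formula gives 221.
- Design effect: DE = 1 + (77 − 1) × 0.01 = 1.76.
- Clustered n per arm: 217.6 × 1.76 = 383, or 221 × 1.76 = 389, against 385 stated.
- Check on power: 385 / 1.76 = 218.75 effective patients per arm gives 79.7%.
- Drop-out: 770 / 0.90 = 855.6, rounded up to 856.

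The stated size reproduces, so the protocol itself applies a design effect of about 1.76.

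**Step 2: effect of a patient-level economic analysis.** For a between-arm difference in means with equal clusters:

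- correct SE / patient-level SE = √DE, with DE = 1 + 76 × ICC;
- actual coverage of a nominal 95% interval = 2Φ(1.96 / √DE) − 1.

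| ICC for costs or QALYs | DE | SE ratio | Coverage |
|---|---|---|---|
| 0 | 1.00 | 1.00 | 95% |
| 0.005 (assumed) | 1.38 | 1.17 | 90% |
| 0.01 (protocol's value, set for injurious falls) | 1.76 | 1.33 | 86% |
| 0.02 (assumed) | 2.52 | 1.59 | 78% |
| 0.05 (assumed) | 4.80 | 2.19 | 63% |

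At ICC 0.01 the intervals have 1 / 1.33 = 75% of the correct width.

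**Step 3: check by simulation.** Five hospitals of 77 patients per arm, normal outcome, ICC 0.01, 4,000 replicates. The true standard deviation of the difference was 0.096 and the mean patient-level SE 0.072, a ratio of 1.33. Coverage of the patient-level interval was 85.4%, in line with the formula.

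**Step 4: would resampling hospitals alone be enough?** In the same simulation the limiting SE of a plain cluster bootstrap was 0.083 against the true 0.096, and its normal interval covered 88.4%. With five hospitals per arm, the bootstrap variance of the arm mean is 4/5 of the unbiased estimate, and a normal quantile is too small for so few clusters. An interval built on hospital means, with the unbiased variance and t on 8 degrees of freedom, covered 95.2%.

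**The case against.** The strongest reply is that the article never says clustering is ignored. A reader might infer an ordinary patient-level bootstrap, but the text says only that bootstrapping techniques will be used. That wording could cover cluster or two-stage resampling, and SUR can be fitted inside such a bootstrap or given a cluster-robust variance. The article is condensed, and the resampling unit is the kind of detail a full protocol or analysis plan may hold. The authors plainly know the design is clustered. This stands, and it makes the point conditional. It does not remove it: the article commits to a named estimator, justified by a different correlation, while neighbouring sections of the same length do name the hospital level.

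Three further limits also stand.

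- The ICC of 0.01 was set for the proportion with injurious falls. Carrying it over to costs and QALYs is an assumption, and a smaller ICC means a smaller loss.
- A reader might suppose that costs cluster through hospital-specific prices. The data-collection section on cost-effectiveness does not support that. It multiplies volumes of care by unit prices without tying them to a hospital, and it counts productivity losses, which the falls clinic does not deliver.
- A reader might lower the coverage further by using a t distribution on 8 degrees of freedom. That does not describe the interval in question, which carries a patient-level SE with about 770 − 2 = 768 degrees of freedom. About 86% is the supported figure at ICC 0.01.

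**Conclusion.** The point holds in conditional form. As named, the economic model and bootstrap contain nothing for the hospital, although hospitals were allocated and the fall and shared-decision-making analyses are multilevel. If both are run on patients and the ICC for costs or QALYs is positive, uncertainty is understated. The size is a factor of about 1.33 in the SE and about 86% coverage at ICC 0.01, and 90% to 63% coverage over the assumed range 0.005 to 0.05. These figures rest on equal clusters of 77 and roughly normal estimates of the cost and effect differences. They describe the components of the ratio rather than the ratio itself.

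The stronger statement, that the planned intervals are definitely too narrow, is not supported, because the resampling unit and the relevant ICC are both unstated. Nothing here shows bias in the point estimates. The primary Cox analysis is untouched, and the section attaches no test or threshold to the ratio. This is a should-fix for a secondary aim.

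**What to change.** State in the analysis plan how the hospital enters the economic analysis:

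- **Model.** Use a cluster-aware bivariate cost-effect model. A bivariate multilevel model with a hospital random intercept would do, as would SUR with a cluster-robust variance corrected for few clusters.
- **Bootstrap.** Resample so that hospitals are respected within arm, with a correction for the small number of clusters, for example a two-stage bootstrap with shrinkage. Simply resampling whole hospitals is not enough with about five per arm (88% coverage in step 4).
- **Outputs.** Derive the uncertainty in the ratios, the planes and the acceptability curves from that procedure, for both the injurious-fall and the QALY comparison.

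The cost is more analysis code, a paragraph in the plan and wider intervals. No new data are needed. If the full protocol or analysis plan already specifies such a method, a clarifying sentence closes the point.
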